# ENABLE-SG (Educate, Nurture, Advise, Before Life Ends for Singapore) as a proactive palliative care model: protocol for a hybrid type 1 effectiveness-implementation randomized wait-list controlled trial

**DOI:** 10.1186/s12904-024-01353-2

**Published:** 2024-01-30

**Keywords:** Cancer, Palliative care, Psychoeducational, Telehealth, Health coaching, Implementation

## Abstract

**Background:**

Specialist palliative care is often provided late in the patient’s disease trajectory in response to uncontrolled symptoms. Shifting from this reactionary illness-stress paradigm to a proactive health-wellness approach, the ENABLE (Educate, Nurture, Advise, Before Life Ends) telehealth model aims to enhance the coping, stress and symptom management, self-care, and advance care planning skills of patients with advanced cancers and their caregivers. The ENABLE model has been culturally adapted to Singapore (ENABLE-SG) and pilot-tested. A hybrid type 1 effectiveness-implementation design will be used to evaluate the effectiveness of ENABLE-SG while collecting real-world implementation data.

**Methods:**

This single-centre, assessor-blind, wait-list (immediately vs. 6 months) randomized controlled trial will recruit 300 adult patients within 60 days of an advanced cancer diagnosis and their family caregivers from the National Cancer Centre of Singapore. ENABLE-SG comprises structured psychoeducational sessions with a telehealth coach, covering essential topics of early palliative care. Participants will be assessed at baseline and every 3 months until patient’s death, 12 months (caregivers), or end of study (patients). The primary outcome is patient quality of life 6 months after baseline. Secondary patient-reported outcomes include mood, coping, palliative care concerns, and health status. Secondary caregiver-reported outcomes include caregiver quality of life, mood, coping, and care satisfaction. Mixed-effects regression modelling for repeated measurements will be used. To assess the effectiveness of ENABLE-SG versus usual care, patient and caregiver outcomes at 6 months will be compared. To compare earlier versus delayed ENABLE-SG, patient and caregiver outcomes at 12 months will be compared. Within the hybrid type 1 effectiveness-implementation design, implementation outcomes will be evaluated in both the early and delayed groups. Acceptability, adoption, appropriateness, and feasibility will be assessed using a feedback survey and semi-structured interviews with a purposive sample of patients, caregivers, and healthcare providers. Transcribed interviews will be analysed thematically. Other implementation outcomes of penetration, fidelity, and cost will be assessed using records of study-related processes and summarized using descriptive statistics. A cost-effectiveness analysis will also be conducted.

**Discussion:**

This study will assess both effectiveness and implementation of ENABLE-SG. Insights into implementation processes can facilitate model expansion and upscaling.

**Trial registration:**

Registered prospectively on ClinicalTrials.gov, NCT06044441. Registered on 21/09/2023.

**Supplementary Information:**

The online version contains supplementary material available at 10.1186/s12904-024-01353-2.

## Background

Worldwide and in Singapore, cancer is a prevalent cause of death [1, 2]. With Singapore’s ageing population and a higher risk of cancer associated with increasing age, the number of people diagnosed and living with cancer is projected to rise [3]. Palliative care addresses the burden of advanced cancer experienced by patients and their families through early identification, assessment, and treatment of physical, psychosocial, and spiritual sources of poor quality of life [4–7]. Both the American Society for Clinical Oncology and the European Society for Medical Oncology recommend that all patients with advanced cancer receive palliative care from the time of diagnosis [8, 9].

Despite guideline recommendations, the current practice of specialist palliative care in Singapore focuses on supporting patients with complex problems in the last weeks of life [10]. Palliative care is often triggered by uncontrolled symptoms during crises, representing a reactive care approach [11, 12]. This approach delays palliative care initiation among patients in their early months of diagnosis when they may still have a reasonably good quality of life without overt symptoms or problems [13–16]. Models of palliative care should shift from the current reactionary illness-stress paradigm to a proactive health-wellness approach that is integrated early in the patient’s serious illness trajectory [17].

The hallmarks of early palliative are symptom management, coping skills development, treatment decision-making, and engagement in advance care planning [18]. Existing models often rely on specialist clinicians in outpatient settings to provide such comprehensive care, posing challenges to scalability and sustainability [19–24]. The ENABLE (Educate, Nurture, Advise, Before Life Ends) telehealth model developed in the United States (U.S.) offers a possibility of engaging non-specialists as health coaches to deliver early palliative care proactively [25–27]. Through structured telephonic sessions, health coaches can coach patients and their caregivers on coping, stress and symptom management, self-care, and advanced care planning skills, empowering them to mitigate and avoid crises. In the U.S., randomized controlled trials showed that compared to usual care, the ENABLE model improved the quality of life of patients with advanced cancer [28]. Patients also experienced additional survival benefits when enrolled early in the ENABLE model, with less depression and lower stress burden among caregivers [29, 30].

Although the ENABLE model has demonstrated effectiveness in the U.S., it is uncertain if the benefits will be transferrable cross-culturally when implemented in Singapore with different organisational, social, and cultural norms [31]. Addressing contextual differences, the ENABLE model has been culturally adapted (ENABLE-SG) through a qualitative formative evaluation. The main modifications made were adding screening questions for concerns salient to the local context and adjusting the content of coaching sessions to be relevant to the local population [32, 33]. The adapted ENABLE-SG was subsequently piloted in 43 patients and 15 caregivers (manuscript in preparation). The pilot study had a completion rate of 72% among patients and 94% among caregivers. Also, the telehealth mode of delivery was found acceptable, with 96% of the sessions conducted over the telephone. These findings demonstrate that ENABLE-SG is feasible and acceptable for further evaluation in the Singapore context.

Using a hybrid type 1 effectiveness-implementation design, this randomized wait-list controlled trial of the culturally adapted ENABLE-SG among patients with recently diagnosed advanced cancer and their caregivers will concurrently assess both effectiveness and implementation outcomes [34]. The simultaneous evaluation of clinical outcomes and implementation processes will facilitate a rapid translation of the model into clinical implementation subsequently to improve healthcare delivery. The specific aims are:Assess the effectiveness of ENABLE-SG among patients with advanced cancer. At 6 months post-enrolment, we hypothesize that, compared to usual care (wait-list controls), patients who received ENABLE-SG will have better health-related quality of life (QoL) [primary outcome], mood, health status, coping strategies, fewer palliative care concerns, less acute healthcare utilisation, and smaller hospital bill [secondary outcomes]. At 12 months post-enrolment, we hypothesize that, compared to those who received delayed ENABLE-SG, patients who received early ENABLE-SG will report better abovementioned outcomes.Assess the effectiveness of ENABLE-SG among caregivers of patients with advanced cancer. At 6 months post-enrolment, we hypothesize that, compared to usual care (wait-list controls), caregivers who received ENABLE-SG will have better health-related QoL, mood, coping strategies, satisfaction with care, and lower caregiving costs. At 12 months post-enrolment, we hypothesize that, compared to those who received delayed ENABLE-SG, caregivers who received early ENABLE-SG will report better abovementioned outcomes.Assess ways to improve ENABLE-SG implementation in the real-world context by assessing its penetration, acceptability, adoption, appropriateness, feasibility, fidelity, and implementation cost.

## Methods/ design

### Study design

This type 1 hybrid effectiveness-implementation randomized wait-list controlled trial will take place in the outpatient setting at the National Cancer Centre of Singapore (NCCS). NCCS serves 65% of all cancer patients in the public sector in Singapore. Patient participants will be randomized to receive the ENABLE-SG intervention immediately (early ENABLE-SG group) or after 6 months (wait-list control group) (Fig. 1). Caregiver participants will be assigned to the same group as the patient care recipient. Patient participants will be followed up until death or the end of the study, whichever is earlier. Caregiver participants will be followed up until the patient’s death or the end of study, whichever is earlier. Figure 2 depicts the study schedule.

**Fig. 1 Fig1:**
[figure not shown]
Study flow chart for trial participants Legend: Participants are randomized to either receive the ENABLE-SG intervention immediately (early ENABLE-SG group) or after 6 months (wait-list control group)

**Fig. 2 Fig2:**
[figure not shown]
Overall study schedule for trial participants

### Participants

A patient will be eligible if he/she is (1) aged ≥ 21 years, (2) within 60 days of being informed of an advanced cancer diagnosis, defined as metastatic or recurrent/ progressive Stage III/IV solid tumour, (3) able to speak English or Mandarin Chinese, and (4) able to provide informed consent. Patients will be excluded if they (1) have a medical record documentation of an active severe mental illness, dementia, active suicidal ideation, uncorrected hearing loss, (2) are unable to complete patient-reported outcome measures, or (3) already known to a hospice or palliative care service. Patients without a caregiver or whose caregivers choose not to enrol may still participate in the study.

A caregiver will be eligible if he/she is (1) aged ≥ 21 years, (2) self-endorsing or identified by the enrolled patient with advanced cancer as an unpaid spouse/partner, relative or friend who knows the patient well, who provides regular support due to their cancer and who does not have to live in the same dwelling, (3) able to speak English or Mandarin Chinese, and (4) able to provide informed consent. Caregivers will be excluded if they are unable to complete caregiver-reported outcomes or have self-reported severe mental illness, dementia, active suicidal ideation, or uncorrected hearing loss.

To assess ways to improve ENABLE-SG implementation, healthcare providers whose patients are enrolled in the study will be invited to participate in semi-structured interviews. They will be eligible if they are aged ≥ 21 years and able to provide informed consent.

### Recruitment

The study team will screen NCCS outpatient clinic lists of participating oncologists for eligible patient participants. Potential patient participants will be approached in the oncology outpatient clinics to verify eligibility and obtain informed consent. Each enrolled patient participant will be asked to identify an eligible caregiver. A study team member will perform either in-person or remote consent-taking with eligible caregivers. Regardless of caregiver participation, the patient can still enrol in the study. Recruitment has started in December 2023.

### Randomization

After consent is obtained, patient participants will be randomized in a 1:1 ratio to the early ENABLE-SG intervention group or the wait-list control group using randomized permuted blocks generated by an independent statistician. The block size is concealed from the study team until study completion. Randomization will be stratified by tumour types (lung, gastrointestinal, breast, and others) to ensure comparable numbers allocated to both study groups. The consent taker will inform the randomizer after obtaining informed consent and administering baseline questionnaires. The randomizer will then notify the consent taker about the allocation status. The randomizer will not participate in any recruitment procedures.

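### Telling the consent taker each allocation exposes the next one to prediction from past ones; release allocations to someone who neither recruits nor assesses

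*Protocol article*

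**What the plan says.** The protocol article (Randomization) allocates patients 1:1 "using randomized permuted blocks generated by an independent statistician", stratified by tumour type in four groups: lung, gastrointestinal, breast and others. The abstract describes a single-centre trial.

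The order of events is also set out there. First, "The consent taker will inform the randomizer after obtaining informed consent and administering baseline questionnaires". Then, "The randomizer will then notify the consent taker about the allocation status". Two further safeguards are stated: "The randomizer will not participate in any recruitment procedures", and "The block size is concealed from the study team until study completion".

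Under Recruitment, the study team screens the outpatient lists of participating oncologists, and "Potential patient participants will be approached in the oncology outpatient clinics to verify eligibility and obtain informed consent".

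The article does not say what the block size is, whether it is fixed or varied, how many people take consent, or whether they share what they learn about allocations.

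**The concern.** Within a stratum of a permuted-block list, the past allocations are exactly the information needed to predict the next one. The notification step hands that information to a person who takes consent. If the block size is fixed, the same record eventually reveals the size as well, so withholding the number protects little.

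There is room to act on a prediction before randomization. Tumour type, which defines the stratum, is likely to be visible when clinic lists are screened. The recruiter chooses whom to approach. Judging whether a patient can complete the outcome measures (an exclusion criterion under Participants) involves discretion, and the 60-day eligibility window allows an approach to be deferred to a later clinic. Obtaining consent and baseline data before allocation does not help here, because the selection would already have happened.

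At stake is the comparability of the arms at entry. The primary outcome is self-reported quality of life (FACIT-Pal) at 6 months, and participants know whether coaching starts now or later, although assessors are to be blinded. If fitter or more receptive patients were steered to immediate coaching, the planned adjustment for baseline score would correct only what that score captures. Analysis by intention to treat does not address selection at entry.

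**Working it through.** The article gives no figure for block size or predictability, so there is none to reproduce.

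**Inputs from the article:** 1:1 ratio, four strata, one centre, 300 patients.
**Assumptions:** block size 2b with b = 2, 3 or 4 (sizes 4, 6, 8); equal strata, 300/4 = 75 patients each.

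**1. Certain assignments, fixed and known size, all earlier allocations seen.** The next arm is certain once one arm has used up its b places in the block. Averaged over all orderings of a complete block, the certain share is 1/(b+1).
- Hand check for size 4: of the six orderings, AABB and BBAA each leave two certain places and the other four leave one each. That is (2×2 + 4×1)/(6×4) = 8/24 = 33.3%.
- Size 6: 1/4 = 25%. Size 8: 1/5 = 20%.
- Simulation with strata of 75 gives 32.4%, 23.8% and 19.2%, slightly lower because the last block in a stratum is incomplete.

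**2. The recruiter sees only a fraction f of allocations.** Assume these are a random subset and, generously, that block boundaries are known. All b allocations to the exhausted arm must have been seen, so the share becomes f^b/(b+1).

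| Size | f = 1 | f = 1/2 | f = 1/3 |
|---|---|---|---|
| 4 | 33.3% | 0.25/3 = 8.3% | 0.111/3 = 3.7% |
| 6 | 25.0% | 0.125/4 = 3.1% | 0.037/4 = 0.9% |
| 8 | 20.0% | 0.0625/5 = 1.3% | 0.0123/5 = 0.2% |

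Simulation agrees: 8.3%, 3.3% and 1.2% for a half; 3.6%, 1.0% and 0.2% for a third.

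**3. Can a concealed fixed size be inferred?** Take an observer who keeps a complete, ordered log by stratum and treats sizes 2, 4, 6, 8 and 10 as equally likely. The true size reaches 95% posterior probability after a median of 38, 35 and 37.5 patients for true sizes 4, 6 and 8 (90th percentiles 57, 50 and 70). As a share of 300, the medians are about 12% to 13% and the largest 90th percentile is 70/300 = 23%.

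**4. Best-guess accuracy, all allocations seen.** For size 4, the chance of guessing right at places 1 to 4 is 1/2, 2/3, 2/3 and 1, so the average is 2.833/4 = 70.8%. Simulation in strata of 75, with an observer who knows the possible sizes:

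| Scheme | Certain | Best guess correct |
|---|---|---|
| Fixed 4 | 32.4% | 70.5% |
| Fixed 6 | 23.8% | 68.3% |
| Fixed 8 | 19.2% | 65.9% |
| Random 4 or 6 | 5.7% | 68.9% |
| Random 4, 6 or 8 | 2.3% | 67.9% |

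Varying the size removes most certainty but leaves the guessing advantage over 50% almost untouched.

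**5. The recruiter never learns past allocations.** Certainty is 0% and guessing accuracy is 50%, whatever the block scheme.

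**The case against.** The strongest objection is that the article does not place this trial in the worst case. A reader might infer from the singular wording that one fixed block size is used, and from the notification step that the recruiter knows every past allocation, and so conclude that a fifth to a third of assignments here are certain in advance. The documents do not support that. A singular block size is common shorthand and is compatible with varied sizes. An article may condense the scheme, and publishing its details would sit badly with hiding them from the study team. Nothing says there is only one consent taker or that allocations are shared. Step 2 shows how much this matters: with half the allocations seen, certainty falls to between 8% and 1%. This part of the objection stands, and it is why the figures are conditional.

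It is also fair that the stated safeguards are real, that both arms eventually receive coaching, which weakens any motive to steer, and that baseline score is a covariate. No bias in FACIT-Pal has been estimated, and nothing here shows that steering will occur.

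One point survives all of this. The notification step is written plainly and needs no inference. It gives allocation history to people who recruit under any block scheme, and none of the listed safeguards acts on prediction from that history.

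**Conclusion.** The point holds as a weakness in the stated notification procedure, not as a demonstrated failure of concealment. The current allocation is well protected; the next one is not protected from inference based on earlier ones.

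The size depends on facts the article does not give. If the block size is fixed at 4 to 8 and known or inferred, and a recruiter sees all allocations, 33% to 20% of next assignments are certain, which is about 100 to 60 of 300 (300/3 and 300/5). If a recruiter sees a random half, the share is about 8% to 1%, or roughly 25 to 4 of 300 (300/12 and 300/80). With all allocations seen, best-guess accuracy is about 66% to 70% for fixed and varied sizes alike. Whether sizes vary is mostly a missing detail. Who is told the allocation is a stated choice, and it can be improved cheaply.

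**What to change.** **Main change.** In the Randomization section, replace the step that notifies the consent taker with wording such as: *The randomizer will release the allocation to the coaching coordinator, who will inform the participant. Staff who recruit or assess patients will not be told the allocation.* The article does not describe a coaching coordinator, so the role must be assigned to a named function outside recruitment and assessment. This removes routine knowledge of past allocations under any block scheme; recruiters may still learn some informally. It would also support the blinding of data collectors promised under Data collection, should consent takers also collect follow-up data.

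**Secondary change, only if the block size is in fact fixed.** Have the independent statistician use randomly varied sizes within each stratum for the allocations still to be made. With sizes 4, 6 and 8 this cuts certain knowledge to about 2%, but it does not reduce guessing, so it does not replace the main change. If sizes already vary, no new list is needed.

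**Cost.** A short amendment and a small change in how participants are told their group. The secondary change would mean switching lists after recruitment has begun and possibly a slightly larger end-of-block imbalance within strata. No extra patients are needed.

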### Usual care prior to delayed intervention

Patients randomized to the wait-list control group will receive usual care for the 6 months before receiving the ENABLE SG intervention. Under usual care, patients are managed by their primary oncologists who focus on cancer-directed treatments. When patients develop complex care needs, the primary oncologist may refer the patient to available palliative care services. Patients and their caregivers may access usual support services such as medical social worker consultations, allied health professional consultations, and support group participation. Data on the utilisation of these other services will also be collected.

### ENABLE-SG intervention

ENABLE-SG closely follows the original ENABLE model with some modifications following cultural adaptation: (1) adding optional discussion topics, (2) assessing preferences for decision-making and tailoring sessions to individual family dynamics, and (3) allowing a flexible mode of delivery [32, 35]. Every patient and caregiver will receive six and four individual structured psychoeducational sessions, respectively, with a health coach. These sessions will be primarily delivered over the phone. Different health coaches will conduct sessions for each patient-caregiver dyad. The topics covered in the sessions are based on essential elements of early palliative care (Table 1) [18]. All sessions will begin with screening for distress using the Distress Thermometer and Problem List culturally adapted from the National Comprehensive Cancer Network (Fig. 3) [36]. From screening results, the health coach can flexibly change the order of the topics to address specific problems and discuss additional topics where relevant. The health coach will aim to conduct the sessions weekly. Most participants from the pilot study could complete the sessions within three months.

**Table 1 Tab1:** Topics and elements of palliative care covered by ENABLE-SG sessions

Patients	Caregivers	Topics covered	Elements of palliative care
**Session 1** Maintaining positivity	**Session 1** Maintaining positivity	• Handling problems with a positive attitude • A problem-solving attitude • The seven steps of problem-solving	• Improving symptom relief and function • Psychosocial and spiritual care
**Session 2** Self-care	**Session 2** Self-care	• Healthy eating and nutrition • Exercise • Quitting smoking • Sexuality • Work and family	Improving symptom relief and function
**Session 3** Coping with stress	**Session 3** Coping with stress	• Coping with stress • Spirituality • Getting the support you need	Psychosocial and spiritual care
**Session 4** Managing symptoms	**Session 4** Managing symptoms	• Managing symptoms • Common symptoms in cancer • Common thoughts and feelings	Improving symptom relief and function
**Session 5** Talking about what matters most and making choices	-	• Talking with your family and healthcare providers • Core values: what matters most • Decision aids: making choices that are right for you	Enhancing communication, values-based treatment, and goals of care conversations
**Session 6** Life review	-	• Starting a conversation about your journey • Looking at today, looking at tomorrow • Creating a legacy	Psychosocial and spiritual care

